### Data collection

All survey data will be collected online, self-reported through the learning management system. Module surveys will be completed by PCP participants from all teams at five time points: before (T1) and after Module 1 (T2), after Module 2 (T3) and Module 3 (T4), and at 6 months following final module completion (T5). For Module 2 and Module 3, the post module survey from the immediately preceding module will serve as the baseline survey. Completion of the baseline measures will be a prerequisite to enrollment in CAPACITI. We will follow the Dillman Tailored Design Method to administer the questionnaire with up to five follow-up emails to non-responders [29].

We will conduct virtual focus groups (30 to 60 min in length) approximately three weeks post module completion with a purposive sample of teams from intervention and control groups: 6 to 10 teams in each arm per module (12 to 20 teams total, representing 60 to 100 team members total). The focus group discussion guide was developed and tested in the CAPACITI pilot [23]. In the focus group we will inquire if implementation was perceived as successful (If so, how? If not, why?) and what were the barriers and facilitators. These data will be supplemented by field notes maintained by staff during the study.

### Statistical power /sample size

Sample size calculation is based on the assessment of the primary outcomes of Effective Care Delivery (ECD 8-items) subdomain on the End-of-life Professional Caregiver Survey (EPCS) and the palliative care identification variable (% of patients identified as requiring a palliative approach to care).

Previous work using the EPCS with nurses, physicians, and social workers identified a mean score of 3.6 for the ECD subdomain and a standard deviation (SD) of 1.0 (scale from 1 to 5) [24]. We assumed that a difference of 0.5 in SD (i.e., a delta of 0.5 or a half point on the scale) between treatment groups at T2 would be important to detect. Accounting for the cluster design, we estimate that the correlation between providers within teams was 0.15 and that each team would have a minimum of 4 members participate. Given a two-sided alpha of 0.05, a power of 80%, 192 providers from 48 teams would be required. This will also allow for detection of a 1-point difference increase of the % of patients identified as requiring a palliative approach to care (SD = 2).

We anticipate 100 PCP teams with an average of 4 members per team, in each module. The teams will be from across Canada and geographically diverse (e.g., rural, urban, and remote), which is critical to generating evidence on generalizability in diverse communities across the country.

### Recruitment

Study participants will be members of PCP teams that enroll in CAPACITI (See Appendix for CAPACITI information sheet). Participants can also sign up as individuals or solo providers. Potential teams across Canada will be informed about CAPACITI through a promotional campaign, including direct solicitation and advertising by our partner stakeholders and organizations, including Pallium Canada, Hospice Palliative Care Ontario, Saint Elizabeth Health Care, Canadian Hospice Palliative Care Association, and provincial professional associations, e.g., Medical Association of Ontario. A team wishing to participate in the program will complete a registration form, indicating the team members that will be participating. Team members will then register individually on the Moodle learning management system to enrol in the program.

### Eligibility

To be eligible the “team” or individual must be community-based and willing to provide palliative care to their patients, defined as managing symptoms, addressing psychosocial needs, educating patients and families, and coordinating care. Teams need to include at least one prescribing clinician (e.g., primary care physician, nurse practitioner). Participates in CAPACITI can include physicians, nurses, social workers, office assistants, patient coordinators, etc. The program will be offered free to teams, with the understanding that those participating will complete the educational and data collection components.

Participants will be strongly encouraged to complete an interprofessional, standardized, evidence-based, education program, namely Pallium Canada’s LEAP course (Learning Essential Approaches to Palliative care), prior to starting CAPACITI. LEAP is the most widely recognized palliative care education program for generalist health care providers in Canada [14, 15, 20]. Some topics include the palliative care philosophy and complex management for common symptoms such as pain, delirium, constipation, depression, grief, etc. The courses are taught in-person, or via fully online or hybrid delivery, by certified program facilitators [16]. Studies have shown that the LEAP courses provide primary health care teams with foundational skills that allow them to integrate primary palliative care in their clinics [18].

### Randomization

The unit of randomization is the team: individuals clustered within teams or the individual themselves as their own team. Teams who register will be randomized to either the intervention or control arm using a permuted block design to ensure groups of equal sizes [30]. Randomization to either the intervention or control arm will occur independently for each module. That is, group allocation for a module does not predetermine that allocation for subsequent modules. Randomization will be stratified by team size (small or large) and location (west, central, or east) to ensure balanced sub-groups. Randomization is performed independently by using a computer-generated sequence. The randomization procedure will be centralized and managed by an independent statistician.

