## Methods

### Study design

We are conducting a prospective cluster randomized controlled trial (cRCT) in which the clusters are primary care practices (teams) randomized to either a Facilitated or Self-Directed model of CAPACITI. This program consists of three distinct education modules, each which will be evaluated separately. The primary comparison will be between the trial arms upon completion of a module to compare effectiveness of the two approaches. Our study will also measure the change in outcomes within the same team, before and after completion of a module. The anticipated completion date of the cRCT is July 2023. Ethical approval for this study was obtained from the Hamilton Integrated Research Ethics Board (#13867) (see https://clinicaltrials.gov/ct2/show/NCT05120154 for approved operating protocol).

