### Study groups

The control group will receive access to the online session slide decks, tools, “cheat sheets”, resources, and assignments. The intervention group will receive the same access to the online session materials but will also be invited to participate in facilitated virtual webinars, that includes a presentation of the session slide deck and open discussion of the content (Fig. 1).*Control group:* Self-Directed – Access to online CAPACITI materials only (no live presented sessions)*Intervention group:* Facilitated – Access to online CAPACITI materials plus each session is presented on a live interactive video conference, including group discussion of the material for adaptation to local context.

We hypothesize that the interactive sessions and opportunity for open discussion offered to the facilitated group in CAPACITI will better assist them to overcome challenges to knowledge translation and implementation, compared to the self-directed group.

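### Clusters are defined as practices, but individuals may be randomised as their own team, so colleagues in one practice can be allocated to opposite arms

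*Protocol article*

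**What the plan says.** All references are to the Protocol article. Study design states that "the clusters are primary care practices (teams) randomized to either a Facilitated or Self-Directed model of CAPACITI", which makes the practice the cluster and treats team as another word for it.

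Randomization sets a different unit: "The unit of randomization is the team: individuals clustered within teams or the individual themselves as their own team". Recruitment opens the same door: "Participants can also sign up as individuals or solo providers". Eligibility admits an individual in their own right: "To be eligible the “team” or individual must be community-based and willing to provide palliative care to their patients". It requires a team to include a prescriber, but sets no condition about whether an individual has colleagues already enrolled.

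Team membership is self-declared: "A team wishing to participate in the program will complete a registration form, indicating the team members that will be participating". Nothing says that list must cover the practice.

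Teams are allocated "using a permuted block design to ensure groups of equal sizes", and "Randomization will be stratified by team size (small or large) and location (west, central, or east) to ensure balanced sub-groups". Practice is not a factor in allocation. Each module is randomised afresh.

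On the contrast between arms, Study groups says: "The intervention group will receive the same access to the online session materials but will also be invited to participate in facilitated virtual webinars". Data analysis takes the team as the unit and describes a two-level model of cluster and repeated measures.

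**The concern.** If the unit that registers is not the practice, one practice can hold several randomised units: two individuals, or an individual beside a team. Each is allocated separately, so both arms can sit in the same office.

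The arms share all written materials. What separates them is the live presentation and discussion, which a facilitated participant could pass on to a self-directed colleague. Module 1 also asks participants to set up a registry of palliative patients (Table 1). Where a practice keeps one registry, the work of a facilitated participant could raise the number identified by a self-directed colleague, and that number feeds a primary outcome. Both routes pull the comparison towards no difference.

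The model would also treat such colleagues as unrelated clusters, although the sample-size section assumes a correlation of 0.15 between members of one team. The Limitations section covers the lack of an untreated arm, lack of blinding and self-report, but not contamination.

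**Working it through.** **1. Does the stated rule allow a split?** Under Study design, two colleagues in one practice form part of one cluster and share an arm. Under Recruitment, Eligibility and Randomization, each may register alone, each is eligible, and each is a unit of randomisation. The strata are team size and region only. A split is therefore allowed.

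**2. How often would it occur, once there are separate registrations?** With 1:1 allocation and k separate registrations treated as independent draws, P(split) = 1 − 2 × (1/2)^k.
- k = 2: 1 − 2 × 0.25 = 0.50
- k = 3: 1 − 2 × 0.125 = 0.75

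Two individuals from one practice would normally fall in the same stratum. If they also fell in the same permuted block, the chance would be higher. For an assumed block of 4 it is 2/3, because two of the three remaining places belong to the other arm. Block size is not stated. Because allocation is redrawn per module, a pair taking all three modules would be split at least once with probability 1 − 0.5³ = 0.875.

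**3. The plan's own sample size.** Inputs from the sample-size section: difference 0.5, SD 1.0, ICC 0.15, 4 members per team, two-sided alpha 0.05, power 80%.
- Design effect = 1 + (4 − 1) × 0.15 = 1.45
- Individually randomised, t-based: 64 per arm
- 64 × 1.45 = 92.8; 92.8 / 4 = 23.2, rounded up to 24 teams per arm
- Total: 48 teams, 192 providers

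This matches the stated 192 providers from 48 teams, so the point does not rest on an arithmetic error.

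**4. Effect of dilution.** Let c be the share of the 0.5-point difference lost to contamination. The documents give no value for c, so 0 to 20% is an assumed range. With n providers per arm, normal approximation:

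Power = Φ(0.5 × (1 − c) / √(2 × 1.45 / n) − 1.96)

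For 192 providers, n = 96 and √(2.9/96) = 0.174. For 400 providers (100 teams of 4, as anticipated), n = 200 and √(2.9/200) = 0.120.

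| c | Difference | Power, 192 providers | Power, 400 providers |
|---|---|---|---|
| 0 | 0.500 | 0.82 | 0.99 |
| 5% | 0.475 | 0.78 | 0.98 |
| 10% | 0.450 | 0.74 | 0.96 |
| 20% | 0.400 | 0.63 | 0.91 |

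These figures keep the plan's 4 members per team and change only the difference.

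**The case against.** The strongest reply is that the article condenses a fuller operating protocol, and that handling several registrations from one site is operational detail which may be settled there. That would answer a complaint about a missing rule. It does not answer this point, because the article states the unit in two places and the two do not agree: Randomization expressly makes an individual a unit.

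A second reply is that individuals and solo providers may be one category, meaning people with no enrolling team. If every individual registrant were truly a solo practice, cluster and practice would coincide and the problem would vanish. The reading is possible, but the article names the two side by side and does not confine individual entry to solo practices.

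Other parts of the case against stand, and they limit what can be claimed:
- A reader might infer that split practices are likely. The documents do not support that. Recruitment describes promotion to teams, an average of 4 members is anticipated, and about 100 teams are spread across Canada.
- A reader might infer that the trial would be underpowered. That holds only at the 192-provider minimum, and only under an assumed loss. At 400 providers power stays at 0.91 or more up to 20% loss.
- A reader might infer that the authors expect a negligible difference. The Limitations section calls that possible, while the Aims and Study groups sections hypothesise that facilitation is better.
- No section says clusters were chosen to keep facilitated content out of the control arm, so the point does not rest on that motive.

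**Conclusion.** The concern holds as an inconsistency in the unit of randomisation, with a consequence that the stated rule permits. Colleagues in one practice can be placed in opposite arms, at about 50% for two separate registrations, and then be analysed as independent clusters. Any facilitated content that passed between them would bias the difference towards zero.

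The size cannot be derived from the documents, because neither the number of such registrants nor the transfer between colleagues is given. Under an assumed loss of 5% to 20%, the 0.5-point difference becomes 0.475 to 0.40. At the anticipated enrolment the attenuated estimate matters more than power, and recruiting more providers would not remove it. A null or small result would then be harder to read, because little benefit of facilitation and shared content would look alike.

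**What to change.** Make Randomization agree with Study design. Suggested wording:

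> The unit of randomisation is the primary care practice. Before each module's allocation, all registrants who share a practice, whether they registered as a team or individually, are combined into one cluster and receive the same arm. A provider with no enrolled colleague in the practice forms a cluster of one.

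To support this:
- Record practice site for every registrant, including individuals. The team form already captures location, so this extends existing data capture.
- Have the independent statistician check for shared sites before each module's allocation, and set the size stratum from the merged cluster.
- Fit the cluster term in the mixed models at practice level.
- Let anyone who registers after their practice has been allocated receive that practice's arm, but leave them out of the primary analysis. Counting them would allow recruitment with the allocation known.

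The cost is one registration field and one check per allocation. The downside is slightly fewer, larger and more unequal clusters, and a few late registrants not counted. If every individual registrant proves to be a true solo practice, the rule changes nothing.

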### Data analysis

The unit of analysis will be the PCP team. Survey (quantitative) data will be used to compare treatment groups with respect to team and individual characteristics (potential covariates) by tabulation methods (means, standard deviations, frequencies). Both team level variables (e.g., region) and member level variables (e.g., palliative care training) will be tabulated. The primary analysis will be a between treatment comparison of intervention and control groups of the change in pre versus post module scores on the primary outcomes (EPCS and % identified for palliative care). Secondary analyses will include comparisons of all team outcomes. Mixed model ANOVA methods will be used, taking into account the increased variance due to cluster randomization, for the assessment of the primary outcomes [30]. Multilevel mixed models with two levels, cluster and repeated measures will be used to investigate the effect of the intervention over time (baseline, post module, 6 months post module).

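### The primary analysis compares pre-to-post change, but the sample size and the design section rest on the post-module score; a baseline-adjusted post-module comparison would align the sections and be more precise

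*Protocol article*

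**What the plan says.** Three sections of the protocol article describe the primary contrast.

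- **Study design** compares the arms when a module ends: "The primary comparison will be between the trial arms upon completion of a module to compare effectiveness of the two approaches". Change appears next, as an addition and within teams: "Our study will also measure the change in outcomes within the same team, before and after completion of a module".
- **Statistical power / sample size** takes half a scale point "between treatment groups at T2 would be important to detect"; T2 is the survey after Module 1. Its SD comes from earlier work that "identified a mean score of 3.6 for the ECD subdomain and a standard deviation (SD) of 1.0 (scale from 1 to 5", which is the spread of a score at one time. For clustering it assumes that "the correlation between providers within teams was 0.15 and that each team would have a minimum of 4 members participate". It gives no SD of change and no pre-post correlation.
- **Data analysis** makes change the primary variable: "The primary analysis will be a between treatment comparison of intervention and control groups of the change in pre versus post module scores". The outcomes named there are the EPCS and the percentage of patients identified. The method is a mixed model ANOVA that allows for clustering; neither baseline nor a stratification factor is named as a model term.

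On allocation, the Randomization section says: "Randomization will be stratified by team size (small or large) and location (west, central, or east".

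**The concern.** A change score and a post-module score have different variances, so a sample size worked out for one does not automatically serve the other. If pre and post scores have equal SDs and correlation r, the SD of change is √(2(1 − r)) times the single-time SD, and it exceeds 1.0 whenever r is below 0.5. In that range the power given in the article is higher than the power of the analysis it calls primary.

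There is also an avoidable loss. Subtracting the baseline fixes its slope at 1. Estimating the slope gives a smaller variance at every r below 1, from data that the trial already plans to collect.

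**Working it through.** **Inputs from the article:** difference 0.5; SD 1.0; ICC 0.15; 4 members per team; two-sided alpha 0.05; power 80%; equal arms; 48 teams required, 100 teams anticipated per module.

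**Assumptions, not in the article:** pre-post correlation r, shown as a range; equal SDs before and after; the same r at team and provider level; the same ICC for each type of score.

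**Step 1: reproduce the stated size.**
- Design effect: 1 + (4 − 1) × 0.15 = 1.45.
- A two-sample t-test for a 0.5 SD difference at 80% power needs 64 per arm.
- 64 × 1.45 = 92.8 providers per arm. Divided by 4 this is 23.2, so 24 teams per arm: 48 teams and 192 providers, as stated.

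The figure is therefore that of a comparison of post-module scores with SD 1.0.

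**Step 2: variance relative to the post-module score.**
- Post-module score alone: 1.
- Change score: 2(1 − r).
- Post-module score adjusted for baseline: 1 − r².
- Ratio of change to adjusted: 2(1 − r)/(1 − r²) = 2/(1 + r), which is above 1 for every r below 1.

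**Step 3: power at 48 teams.** With 24 teams (96 providers) per arm, the standard error is √(2 × 1.45 × factor / 96). For the post-module score this is 0.174, so 0.5/0.174 = 2.88. Power comes from the noncentral t distribution with 46 df.

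| r | Post only | Change | Baseline-adjusted | Variance ratio, change / adjusted |
|---|---|---|---|---|
| 0.3 | 80% | 66% | 84% | 1.54 |
| 0.5 | 80% | 80% | 90% | 1.33 |
| 0.7 | 80% | 95% | 98% | 1.18 |

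**Step 4: teams needed for 80% power** (23.2 × factor, rounded up, times 2).

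| r | Change | Baseline-adjusted |
|---|---|---|
| 0.3 | 66 | 44 |
| 0.5 | 48 | 36 |
| 0.7 | 28 | 24 |

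**Step 5: power of the change score at 100 teams** (200 providers per arm, 98 df): about 83% at r = 0, 90% at r = 0.2, 94% at r = 0.3 and 98% at r = 0.5.

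**Step 6: different r at the two levels.** The factor 1.45 × 2(1 − r) becomes 4 × 0.15 × 2(1 − r_team) + 0.85 × 2(1 − r_provider). With r_provider = 0.3:
- r_team = 0.5: 0.60 + 1.19 = 1.79, power 72% at 48 teams.
- r_team = 0.8: 0.24 + 1.19 = 1.43, power 81%.

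The 66% therefore depends on r being equally low at both levels.

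**The case against.** The strongest reply is that a change-score comparison is valid and, at planned enrolment, well powered. Both parts stand. Under randomisation the expected between-arm difference in change equals that in the post-module score, so the 0.5-point target applies to either. The 66% needs enrolment at less than half of the anticipated 100 teams together with a low r at both levels. A reader might infer from the mismatch that the trial is underpowered or its primary estimate biased; the article supports neither.

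The wording in Study design can also be read as saying when the arms are compared rather than which variable is compared. That softens the conflict there. It does not help the sample-size section, which uses a single-time SD.

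A further reply is that model terms belong in an analysis plan that is not shown. This is right for the stratification factors. One might infer that the plan excludes them or excludes baseline, but the article says neither; it lists team size and location among the covariates to be examined. Their absence from the stated model is no error in itself, and their gain cannot be computed from the article. The reply does not reach the main point, because the article itself fixes change as the primary variable.

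Finally, Modules 2 and 3 take the preceding post-module survey as baseline. This does not count specially against the change score, since either method uses that same variable.

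**Conclusion.** The point holds as one of consistency and precision. The stated 80% at 48 teams belongs to a post-module comparison. With a common r at both levels, it carries over to the change score only if r is at least 0.5, a value that the article neither states nor supports. At assumed r = 0.3, 0.5 and 0.7, baseline adjustment adds about 18, 10 and 2 percentage points of power over the change score at 48 teams; with the same r at both levels it lowers the variance by the factor (1 + r)/2. The practical stake is small if 100 teams enrol and respond, and grows as the analysed number falls towards 48. The change is worth making because it costs almost nothing and leaves one primary contrast throughout.

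**What to change.** Make the primary model a mixed model of the post-module score on arm and the module's baseline score, with team size and location (the stratification factors) as covariates and a random team effect. Name this contrast as primary in the design, sample-size and analysis sections, and report change scores descriptively. The 48-team calculation can then stay: under the assumptions above, the adjusted analysis needs no more teams than that at any r.

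The cost is wording only, since baseline scores and strata are already collected. One small downside remains. A completed baseline is a condition of enrolling in the programme, but the baseline for Modules 2 and 3 is the preceding post-module survey, so some values may be missing. The change score would lose the same values.

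### The primary analysis is described at team level with no member level, so non-response that is selective and differs between arms can bias the pre-post contrast

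*Protocol article*

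**What the plan says.** All references are to the protocol article.

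- **Data analysis.** "The unit of analysis will be the PCP team". The primary analysis is a "between treatment comparison of intervention and control groups of the change in pre versus post module scores on the primary outcomes", named there as EPCS and the percentage identified for palliative care. Mixed model ANOVA allowing for the clustering is to be used for the primary outcomes. The model for effects over time is described with two levels, cluster and repeated measures; the individual provider is not one of them.
- **Study design.** "Our study will also measure the change in outcomes within the same team, before and after completion of a module".
- **Data collection.** "Completion of the baseline measures will be a prerequisite to enrollment in CAPACITI". There are five survey time points, T1 to T5. Non-responders receive up to five follow-up emails. For Modules 2 and 3, the survey after the preceding module serves as baseline.
- **Eligibility.** Participants may be physicians, nurses, social workers, office assistants or patient coordinators. They take part on the understanding that they will complete the data collection.
- **Statistical power /sample size.** The trial is sized in providers, with a within-team correlation: "Given a two-sided alpha of 0.05, a power of 80%, 192 providers from 48 teams would be required".

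**The concern.** T1 covers every enrolled member. T2 covers whoever answers. If the team is the unit and change is the outcome, the literal reading subtracts a mean over all members from a mean over responders. A team that loses a low scorer then appears to improve, and a team that loses a high scorer appears to worsen, although nobody has changed. Teams mix professions, so the level of a member who stops answering may well differ from that of the members who stay.

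Modules 2 and 3 are open to the same problem at both ends. Their baseline is itself a post-module survey, so a member can miss one survey and answer the next.

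What is at stake is the primary comparison. One arm is invited to live sessions and the other is not (Study groups), and participants know their arm (Limitations). Who keeps answering could therefore differ by arm, and a difference in who answers would be read as an effect of facilitation.

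**Working it through.** **Inputs from Statistical power /sample size.** Target: "a delta of 0.5 or a half point on the scale) between treatment groups at T2 would be important to detect". Level and spread: "a mean score of 3.6 for the ECD subdomain and a standard deviation (SD) of 1.0". Clustering: "the correlation between providers within teams was 0.15 and that each team would have a minimum of 4 members participate". Two-sided alpha is 0.05 and power 80%.

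**The plan's own figure.** Design effect = 1 + (4 − 1) × 0.15 = 1.45. A two-sample t-test for 0.5 SD needs 64 per arm. 64 × 1.45 = 92.8, and 92.8 / 4 = 23.2, so 24 whole teams per arm: 48 teams and 192 providers, as stated. (The normal approximation gives 63 per arm, 91.35 after inflation, hence 46 teams and 184 providers.) The calculation contains no term for non-response.

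**One team of four, no true change.** Within-team SD = √(1 − 0.15) = 0.92.

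- Lowest scorer leaves: the expected minimum of four is 1.03 SD below the mean, so 1.03 × 0.92 = 0.95. The mean of the remaining three rises by 0.95 / 3 = 0.32.
- Lowest two leave: the mean rises by 0.61 (simulated).
- Random loss of one: shift has mean 0 and SD 0.92 × √(1/3 − 1/4) = 0.27.
- Random loss of two: SD 0.92 × √(1/2 − 1/4) = 0.46.

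These are shifts in a single team's change. The 0.5 target is a difference between arms, so they cannot be set directly against it.

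**Between arms.** If a fraction p of members stops answering and leavers score g lower than stayers at baseline, the arm's apparent change is about p × g. The bias in the contrast is about (p_int − p_ctl) × g. Simulation used 24 teams of 4 per arm, total SD 1, ICC 0.15, no true effect and 2,000 replicates. Assumed: the rates, the gap g, and a 0.7 stability of the member's residual.

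| Non-response, facilitated vs self-directed | g | (p_int − p_ctl) × g | Simulated bias | Type I error |
|---|---|---|---|---|
| 30% vs 30% | 1.0 | 0 | about 0 | 5.6% |
| 30% vs 20% | 0.5 | 0.05 | 0.05 | 6.0% |
| 40% vs 20% | 0.5 | 0.10 | 0.09 | 8.3% |
| 30% vs 20% | 1.0 | 0.10 | 0.10 | 10.6% |
| 40% vs 20% | 1.0 | 0.20 | 0.18 | 24% |
| 50% vs 20% | 1.0 | 0.30 | 0.27 | 41% |

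Simulated values fall slightly below the formula because teams with no responder drop out. At 50% the mean fraction lost among remaining teams is (0.5 − 0.5⁴) / (1 − 0.5⁴) = 0.467. At 20% it is (0.2 − 0.2⁴) / (1 − 0.2⁴) = 0.199. The difference is 0.27.

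In the first row each arm shows a spurious change of about 0.30, which cancels in the contrast. To reach 0.5 between arms, the formula needs, for example, 50% against 0% with g = 1.0, or a 25-point difference in non-response with g = 2.0.

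**Same members at both times.** In every scenario above the bias was about 0 and the type I error about 5%. That result depends on leavers differing in their stable level. Where non-response depended on the recorded baseline score, a raw same-member change was off by −0.02 to −0.07 through regression to the mean, and the responders-only team change by about 0.06 to 0.14.

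**The case against.** The strongest reply is that the article never says a team score is a mean over whoever responds. The sizing in providers with an ICC, the mixed model ANOVA that allows for clustering, and the individual registration of members (Recruitment) all fit an analysis of individual responses. How scores are formed and how missing data are handled are commonly left to the analysis plan or the full protocol.

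Much of this stands. The point cannot be that the trial will compare different people, only that the stated analysis allows it. Silence on missing data is not held against the article. What remains is text that is present: a team unit, a change outcome, and a level structure that omits the member. An analysis plan that follows those words inherits the problem.

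Three stronger readings are tempting and are not supported.

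- A reader might infer that drop-out alone can manufacture the effect the trial seeks. The 0.5 target is a between-arm difference at T2; similar non-response in both arms cancels, and only extreme imbalance reaches 0.5.
- A reader might infer that follow-up surveys are optional. The article asks participants to complete data collection and pursues non-responders; it only anticipates that some will not answer.
- A reader might infer a compulsory baseline in every module. That is stated for enrolment, so the contrast between a complete baseline and an incomplete follow-up is clear only for Module 1.

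Solo participants, who are allowed, cannot change in composition, which dilutes the effect.

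**Conclusion.** The concern holds in a limited form. Data analysis fixes the team as unit, change as the primary contrast and a longitudinal model without a member level, while Data collection anticipates non-response after a compulsory T1. Followed literally, this lets a team's two values rest on different members.

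The consequence is a possible bias of roughly 0.05 to 0.27 points against a 0.5-point target, with type I error between about 6% and 41%. These figures assume 30% to 50% non-response against 20%, a leaver gap of 0.5 to 1.0 point, and team means over responders. None of these assumptions comes from the documents. If non-response is equal and equally selective in both arms, the bias is near zero. The anticipated 100 teams would not reduce the bias; they would shrink the standard error around it. No size is offered for the percentage identified, because the article does not say how a team's percentage would be formed.

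**What to change.** In Data analysis, replace the team-unit wording with an analysis of member-level responses nested in teams:

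- a team random effect, a member level in the longitudinal model, and the member's own baseline in the model;
- every member kept in the arm to which the team was allocated for that module;
- an explicit statement that a full-team baseline mean is never subtracted from a responders-only post mean.

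Report non-response by arm, profession and baseline score. Add a sensitivity analysis, such as same-member change or teams with complete follow-up. A raw same-member change should not be the sole analysis, because it is affected by regression to the mean when non-response depends on the baseline score.

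This matches the plan's own sizing in providers with an ICC and needs no new instrument, since members register individually and surveys are collected through the learning management system. The cost is slightly more analysis work. Bias from non-response that depends on unobserved outcomes remains.
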